#### Initial contact by the pharmacist

After a brief review of the patient's electronic medical record (EMR) and information supplied in the MMT, the pharmacist attempted to contact the patient. Often multiple attempts (e.g., leaving messages, calling back at a more appropriate time) were required before talking to a patient. After describing details of the program, the pharmacist invited the patient to participate. If a patient indicated interest in participating, a phone or in person intake encounter was scheduled. Additionally, after a patient agreed to participate in the intervention, the pharmacist mailed a welcome packet to the patient. The packet included an introduction letter from the pharmacist and educational materials, including instructions for home monitoring and documents to record blood pressures and action plans. Information on the patient's current medications was occasionally also included in the packet.

After five attempts to reach a patient without making any contact whatsoever, the patient was considered unreachable and a note was placed in the EMR stating that the patient was eligible for the program but could not be reached to assess interest in the program. If a patient was reached but declined to participate, a few questions were asked to ascertain the reason(s) for declining and to obtain basic sociodemographic information. Pharmacists also notified providers, via a note in the electronic medical record, when a patient declined to participate in the program.

#### Encounters with the pharmacist

Encounters took place in clinic settings or by phone. A patient who had access to a home blood pressure cuff and was willing and able to monitor at home could choose to have encounters via phone, otherwise encounters occurred in the clinic. Blood pressure monitors were a covered benefit at VA sites and pharmacists facilitated obtaining one for VA patients who did not already have one. At KP, if patients did not have a home monitor, information was provided about how to obtain and use one.

Pharmacists were provided with an outline (or 'road map') during the training session as a guide for structuring the flow of an intake encounter and as a tool to reinforce motivational interviewing principles and techniques. [See Additional file 1.] The roadmap was reviewed regularly at biweekly conference calls or webinars among all participating pharmacists and study staff during the early part of the intervention when pharmacists were becoming familiar with this behavioral counseling approach and the study protocol. As expected, as the study progressed each pharmacist modified the roadmap slightly (e.g., changed wording of example questions) to follow their own personal style.

During each encounter, the pharmacist worked on developing rapport with the patient and establishing an environment of collaboration, mutual respect, and trust. Additionally, following the MI approach, pharmacists strived to be nonjudgmental, empathetic, and encouraging. Adherence was assessed at every encounter by using a standard adherence question (*In the last week, how many days did you miss one or more doses of your medication*?) and at the intake encounter by assessing adherence for each prescribed hypertension, lipid, and dm medication (e.g., *Can you tell me how you are taking your atenolol?*). Barriers to taking these medications were explored as well. After assessing adherence, recent clinical indicators (blood pressure, A1c, and LDL) were discussed. This discussion included a comparison of the patient's recent numbers with their target numbers. If the encounter was in-person, a blood pressure was measured by the pharmacist (or medical assistant (MA) at KP) as per standard JNC-7 protocols [3]. Labs were ordered according to the treatment algorithms.

Following the assessment and discussion of clinical indicators, the pharmacist elicited the patient's goals and values and talked with the patient about how taking medications might interfere and support those goals and values. Then, based on the information available, the pharmacist evaluated whether the patient had any adherence issues. If not, and poor control persisted, the pharmacist explored with the patient the option of medication change as a means to better control blood pressure. Hypertension medication changes were made using locally approved medication algorithms. Conversely, if the information gathered suggested that adherence issue(s) still persisted, the pharmacist elicited the patient's idea(s) for improving medication adherence.

The patient identified a general target behavior (e.g., remember to take medications, increase exercise) and then ambivalence was explored, by considering the pros and cons of the behavior change, with the patient. Facilitating patient's full exploration of both sides of the behavior enhances the patient's understanding, motivation, and importance of the target behavior. The patient's readiness to change was then assessed using a readiness ruler (with 0 indicating the patient is not at all ready to make the change and 10 indicating the patient is completely ready to make the change). If appropriate (i.e., patient's readiness score > = 7), a specific, short-term action plan was constructed by the patient (e.g., pick up new blood pressure medication at pharmacy on Tuesday and take it three times a day with meals; monitor blood pressure 2 times each day [once in AM and once in PM]; walk on the treadmill 30 minutes on Monday, Wednesday, and Friday mornings). Possible barriers to completing the action plan and solutions to overcome any barriers were then discussed. If a patient was not ready to make a behavior change, a next step was considered (e.g., think about adding a blood pressure medication and discuss at next encounter if blood pressure remains high). At the end of the encounter, the pharmacist summarized the action plan or next step and scheduled a follow-up encounter. Follow-up appointments were to be scheduled weekly if adherence issues were being addressed and every three weeks if medication changes were being made. In practice, patients and pharmacists negotiated appointments based on these factors and convenience to the patient. All encounters were documented in the EMR. Follow-up encounters focused primarily on assessing medication adherence (including barriers to adherence), review of progress on prior action plans, additional action planning, and, when appropriate, intensification of medications.

#### Discharge Criteria

A patient was eligible for discharge from the program when the following criteria were met:

1. Medication adherence issues addressed

2. Home BP or clinic BP, measured by pharmacist or MA, at target [defined for VA patients as average <135/80 and for KP patients as average <130/80 - based on VA vs. KP blood pressure guidelines]; or a diastolic blood pressure <60; or on maximum blood pressure medications

3. On at least a moderate dose statin, if a candidate for statin therapy

4. Glycemic control addressed (KP pharmacists made initial adjustments to hypoglycemic medications if A1c was above target and adherence was appropriate, then referred back to PCP; VA pharmacists referred to PCP or case manager for glycemic medication management after adherence issues were addressed)

Additionally, patients were discharged from the program if they were lost to follow-up (e.g., no showed for three scheduled encounters), enrolled for 6 months without achieving blood pressure target (and no progress in any area was being made), or declined further participation. Providers were notified via a note in the electronic medical record when a patient was discharged from the program as well as when a patient initially enrolled and when medication changes were being made.

#### Reentry

Patients who had been previously discharged but who met the eligibility criteria (i.e., poor BP control with adherence gaps and/or insufficient medication intensification) in subsequent quarters were allowed to reenter the program for additional adherence and/or intensification assistance; however, a three month window was required before reentry (e.g., patients discharged in the second quarter of the intervention period and eligible again in quarter 3 could not reenter in quarter 3 but, if still eligible in quarter 4, could reenter then).

### Intervention Fidelity

As mentioned above, each pharmacist participated in an intensive motivational interviewing training course prior to delivering the intervention to eligible patients. During the intervention period, fidelity was assessed and MI strategies and techniques were reinforced during biweekly webinars, two self-evaluations (completed at month 6 and month 11), and a one-on-one booster session. The booster session occurred approximately six months after the intervention started and consisted of an expert in motivational interviewing observing one or two phone encounters of each pharmacist and providing immediate feedback. A rating form, modified from Resnicow's 1-Pass Coding System for MI[42] was developed for use during the one-on-one observations.

### Data Sources

Data from the following sources will be included in analyses: Automated data systems, MMT, and survey (baseline and follow-up). Additionally, data sources for the implementation evaluation include: patient interview data (VA), key informant interview data (VA; pharmacy managers only in KP), and pharmacist interviews (KP; VA) and observations (VA).

### Outcome Measures

#### Primary Outcome

The primary outcome is the relative change in systolic blood pressure measurements over time as recorded at the point of care in VA and KP electronic databases (excluding blood pressures measured by the AIM pharmacists). As this is an effectiveness study, change in each group will be assessed by the comparison of a precision weighted average of the values obtained during routine outpatient clinical practice in 6 month windows preceding and following the intervention period. The 6 month windows placed on either side of the intervention period ensure that a positive finding of the study would suggest a persistent effect on BP and not just a transient effect during the intervention. Secondary outcomes are described in Table 1.

**Table 1 T1:** Secondary Outcomes

*Description*	*Time period*	*Planned analyses*
*A1c *Change in the percentage of eligible patients with an average A1c > 8%	6 months preceding and following intervention period	Hierarchical logistic regression with a dichotomous dependent variable indicating whether each patient on a team is in control or not in each of the baseline and post intervention periods. The cluster identifier is the team, and the analysis will be stratified by site with fixed site effects. Using an analogous model, the primary hypothesis will be tested by examining the interaction between the treatment group variable and the time period variable at the laboratory measurement level.

*LDL *Change in the percentage of eligible patients with an LDL-c >100 mg/dl	6 months preceding and following intervention period	[See A1c]

*Medication Adherence *Change in rates of poor adherence (>20% gap days)	12 months preceding and following intervention period	Regression with a logit link and binomial error term

*Medication Intensification *Count of medication intensification events for BP, lipid, and hypoglycemic therapy [intensification event defined as 1) an increase in the dose of at least one medication or 2) the addition of another medication, or both]	During intervention period	Negative binomial regression

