### Medication Management Tool (MMT)

A key tool used in the intervention was the Medication Management Tool, a database developed by the study team to assist the pharmacist in tracking and scheduling patient contacts and encounters, assessing medication adherence, providing adherence counseling, making short-term action plans with patients, and collecting data. Key components of the MMT included a summary of refill gap information (e.g., % gap in past year, gap days before each fill) for each blood pressure, blood sugar, and lipid medication prescribed at the time of eligibility, a detailed listing of these medications, daily doses, questions to document pharmacist assessment of medication adherence and reasons for non-adherence to these medications, if applicable. The MMT also included sections for: 1) recording BPs taken at home by the patient and clinical blood pressures taken by the pharmacist (KP and VA) or medical assistants (KP only); 2) documenting patient's goals and values and how medications support or interfere with their goals and values; 3) assessing a patient's readiness to change, exploring ambivalence (if appropriate), and eliciting the patient's action plan or next steps, including barriers and solutions to the plan or steps; 4) documenting whether medications were changed during the visit because of adherence issues or other issues; and 5) if appropriate, recording the reason the patient was discharged from the intervention. See Figure 3 for the first MMT screen pharmacists saw at the beginning of the first encounter with an individual patient.

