It was felt to be important to use blood pressures obtained through routine care to assess the impact of the intervention, again to maintain comparability to the control group who would otherwise have to be invited for special visits to measure their baseline and post-intervention blood pressures. As the number of measurements may vary and thus provide more or less precise estimates of the two endpoints, it is not possible to simply construct a difference between the average pre- and post BPs. We will use all data when multiple measurements allow us to estimate a change in BP more precisely as well as those observations in which only 1 measurement occurs in each period with weighting to reflect the varying precision of the estimates.

A three-level multilevel model will allow us to do this with the multiple individual BP measurements (both pre and post intervention) at level 1 nested within patient identifier at level 2 and team at level 3. An indicator variable will represent whether the BP is from the pre or post period coded so that the coefficient estimates the change in mean BP for the control group. The coefficient of an indicator variable representing treatment teams will estimate the mean BP difference between treatment and controls in the baseline period. The primary hypothesis will be tested by an interaction term between the treatment group indicator and the time period indicator variables. The multilevel structure of the model will account for the varying precision with which the BP endpoints are estimated and the clustering of patients within teams. Site will be included as a fixed variable.

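### The blood pressure exclusion is defined by who took the reading, so it misses readings taken by medical assistants at KP program encounters

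*Protocol article*

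**What the plan says.** The Primary Outcome section takes systolic blood pressure from the VA and KP electronic databases, "excluding blood pressures measured by the AIM pharmacists". Its next sentence restricts the comparison to "values obtained during routine outpatient clinical practice in 6 month windows preceding and following the intervention period". The section on design issues gives the reason, which is comparability with the control group: "It was felt to be important to use blood pressures obtained through routine care to assess the impact of the intervention".

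Three other sections describe who measures blood pressure in the program:

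- The Medication Management Tool (MMT) section lists, among the data recorded, "clinical blood pressures taken by the pharmacist (KP and VA) or medical assistants (KP only").
- Under Encounters with the pharmacist, at an in-person encounter "a blood pressure was measured by the pharmacist (or medical assistant (MA) at KP) as per standard JNC-7 protocols".
- The Discharge Criteria refer to "Home BP or clinic BP, measured by pharmacist or MA, at target".

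The encounters section adds: "All encounters were documented in the EMR". The design issues section also plans a secondary analysis of blood pressure after activation, comparing the arms in the first and second three months. It gives no separate rule on which readings count.

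**The concern.** The exclusion serves to keep program measurements out, so that both arms are measured in the same way. It does this by naming the person who measured. Wherever the protocol describes program readings at KP, it names medical assistants alongside pharmacists, but the exclusion leaves them out. A reading taken by a medical assistant at a KP program encounter is therefore not removed by the rule as written.

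Control patients have no AIM encounters, so such readings can arise in one arm only, at two of the five sites. They follow a stated measurement standard and a program schedule, neither of which is described for routine readings. Any systematic difference between the two kinds of reading would enter the treatment contrast. Program readings could also make up most of the data of a patient who attends often in person.

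**Working it through.** **The plan's own figure.** The only related figure is the detectable difference of 4.4 mmHg at power 0.8, with 275 patients per team, 8 teams per arm and an intraclass correlation of 0.02.

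- Design effect: 1 + 274 × 0.02 = 6.48.
- Effective number per arm: 8 × 275 / 6.48 = 339.5.
- The article states neither the standard deviation nor alpha. Assuming two-sided 0.05 and a normal approximation, the implied standard deviation of change is 4.4 / [(1.960 + 0.842) × √(2/339.5)] = 20.5 mmHg.

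The figure can only be inverted in this way, not confirmed. Nothing in this point changes it; it serves below only as a yardstick.

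**Timing, primary outcome.** The pre-window precedes the program and holds no program visits. The post-window starts after month 14. Enrollment runs through month 14, and no end to encounters at that month is stated. Discharge at 6 months applies only when the target is not met and there is no progress, so it is not a general limit. For an illustrative 6-month episode starting at month s, the overlap with the post-window is max(0, s + 6 − 14) months:

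| Start (month) | Overlap (months) |
|---|---|
| 0, 3 or 6 | 0 |
| 9 | 1 |
| 12 | 4 |
| 14 | 6 |

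Only late KP episodes can reach the post-window.

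**Activation analysis.** Its two 3-month periods coincide with program contact. An upper-end sketch for a KP patient seen only in person, with every reading taken by a medical assistant, runs as follows.

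- Scheduled follow-up is weekly or every three weeks. Over 13 weeks that is 13/1 = 13 or 13/3 ≈ 4 program readings.
- Routine readings: the sample size section works with 2 per 6-month window, so about 1 per 3 months.
- Program share of that patient's readings: 4/(4 + 1) = 0.80 to 13/(13 + 1) = 0.93.
- Shift in the contrast = share × difference between program and routine readings × fraction of the intervention arm affected.

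The difference (3 to 5 mmHg) and the fraction affected are assumptions:

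| Fraction affected | Low | High |
|---|---|---|
| 5% | 0.80 × 3 × 0.05 = 0.12 mmHg | 0.93 × 5 × 0.05 = 0.23 mmHg |
| 20% | 0.80 × 3 × 0.20 = 0.48 mmHg | 0.93 × 5 × 0.20 = 0.93 mmHg |

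**How plausible the fractions are.** Three sites have two intervention teams and two sites have one. The two KP sites therefore hold 2 to 4 of the 8 intervention teams, or 25% to 50% of the arm if teams are of equal size. An affected fraction of 20% of the arm means 40% to 80% of KP intervention patients; 5% means 10% to 20%.

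**Primary outcome, same logic.** Suppose medical assistants' program readings made up 1%, 5% or 10% of the intervention arm's post-window readings and differed by 2 to 10 mmHg (all assumed). The shift would be 0.02 to 0.10, 0.10 to 0.50 or 0.20 to 1.00 mmHg. The last value is 1.00/4.4 = 23% of the detectable difference.

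**The case against.** A reader might infer that these readings stay in the primary outcome and bias it. The documents do not support that. The sentence after the exclusion admits only routine outpatient values in windows outside the 14-month period, and a program reading is hard to call routine, whoever took it. This stands, and it removes most of the exposure. It does not close the gap. If the routine-care wording alone kept program readings out, the pharmacist exclusion would be unnecessary. The Settings section also says the program was treated as a standard quality improvement clinical program, so an analyst could class a medical assistant's reading in a KP clinic as routine.

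It is also not shown that these readings were stored as extractable blood pressures without a program label. They are described as entered in the MMT, and documentation of encounters in the medical record does not settle the matter. This stands as an unknown. Extraction detail, including the source of readings for the activation analysis, may properly sit in a fuller plan. But the rule that the article does state is too narrow, and it is the one most likely to be carried over.

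The sketch for the activation analysis uses high-end inputs. Patients with a home cuff could choose phone encounters, appointments were negotiated in practice, KP pharmacists took some readings themselves (already excluded), and patients who were never reached or who declined have none. All of this stands and pulls toward the lower rows. In the other direction, the formula weights patients equally, and an analysis of individual readings would give frequent attenders more weight.

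**Conclusion.** The point holds as a defect in how the exclusion is defined. The rule names the measurer where its purpose calls for naming the encounter, and so does not exclude readings by KP medical assistants that can exist only in the intervention arm.

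For the primary outcome, the exposure is limited to KP visits continuing past month 14, and is smaller still if such readings are not counted as routine practice. A claim that the primary result is biased would go further than the text allows. The main exposure is the activation analysis.

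The size is not derivable. The share of readings taken by medical assistants, the difference from routine readings and its direction are all unknown. With an assumed difference of 3 to 5 mmHg and a program share of 80% to 93% among affected patients, the activation contrast moves by about 0.1 to 0.2 mmHg at 5% affected and 0.5 to 0.9 mmHg at 20%. The 20% case requires 40% to 80% of KP intervention patients to be affected, so it is a high-end value. No sample size figure changes.

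**What to change.** Define the exclusion by encounter: drop every blood pressure recorded at an AIM program encounter, whoever measured it, and state that this applies to both the primary and the activation analyses.

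The added step is needed only at KP. By the protocol's account, medical assistants took program readings only there, and pharmacist readings at VA are already excluded. Matching KP readings to MMT encounter records would identify them; the MMT is already a listed data source. Limiting the link to KP also avoids the consent that VA patients had to give before their MMT data could be used for evaluation.

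The cost is one sentence, a small linkage step and the possible loss of a few routine readings taken on the same day as an encounter. Quarterly re-eligibility should be left as it is: it determines who re-enters a clinical program, and patients are analyzed in the group assigned when they first became eligible.

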### Intervention

The intervention period was defined as the 14 months in which eligible patients were being identified and offered encounters with the pharmacists. Enrollment of patients occurred during months 1-14. Eligibility for the intervention was determined at the beginning of the 14-month intervention period and again at 3, 6, 9, and 12 months. At the start of each quarter, pharmacists received a list of patients with poor blood pressure control and adherence problems or inadequate medication intensification. The list was randomized within 3 blood pressure strata (> = 160, 150-159, 140-149) to allow outreach to the patients with higher blood pressure levels first. The data were then loaded into the tool used by the pharmacists (MMT) described above. Pharmacists were instructed to contact patients in the order that they appeared on their list. At the end of each quarter, if no attempts had yet been made to contact a patient (i.e., the size of the pharmacist's current patient panel was such that the pharmacist did not have time to contact that individual as well as individuals further down the list), that patient was removed from the pharmacist's list.

Prior to being contacted by the pharmacist, patients at the VA sites were notified via a letter mailed by the study team that a pharmacist would be contacting them to invite them to participate in a new clinical program, a customary VA practice for new projects and programs, and therefore required by the governing IRBs. This letter was not required by the IRB governing the KP sites because patients in KP are accustomed to being contacted by the health plan for clinical outreach.

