We want to be able to describe reasons for the diminution or failure of the intervention to reduce blood pressure relative to effect sizes seen in the prior efficacy studies, particularly if those factors are amenable to changes in protocol that could ameliorate their impact. While it is possible that a successful intervention will show persistence of effect into the 6 month post-intervention window, it is possible that we will lose some power to detect an effect by sample loss if patients do not have recorded blood pressures during that period. Furthermore, some patients will have received the intervention early in the course of the intervention period and thus may be as much as 1 year out from the intervention when the 6 month post-intervention period ends and would have become eligible for repeat enrollment and improvement in the blood pressure if the intervention were an ongoing program at the site.

Therefore, a secondary analysis will examine the blood pressure slope starting at the point where patients are activated (initiation of contact for the intervention). Blood pressure changes will be looked at as a function of time after activation. As the activation is determined by random sampling from the list of eligible cases (within systolic blood pressure groups), the entire control group can be used for comparison with their activation date being randomly assigned during the quarter in which the controls meeting eligibility criteria are identified. We will compare the amount of decrease in blood pressure between the intervention and control groups in both the first and second 3 month periods following activation.

A second reason for lack of effect may be that substantial numbers of patients are not willing to participate in the intervention. It is important to quantify this rate of refusal, as well as to try to estimate the effect of the intervention among compliers so that we can assess whether our intervention achieved similar benefits to prior studies among comparable populations of compliers. A naive as-treated analysis is clearly flawed as the comparability between intervention and control groups is lost when we only analyze those patients in the intervention who accepted the intervention. Thus we will carry out a complier average causal effect (CACE) analysis in which the randomization is used as an instrument to estimate the effect of the intervention among the complier population in both the intervention and control group [43].

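### The calendar-fixed 6-month post window does not ensure that a positive primary result reflects a persistent effect, because patients are activated right up to the day it opens

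*Protocol article*

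**What the plan says.** The Primary Outcome section compares routine-care systolic pressure in a 6-month window before the intervention period with a 6-month window after it, leaving out readings taken by the study pharmacists. It then says: "The 6 month windows placed on either side of the intervention period ensure that a positive finding of the study would suggest a persistent effect". The sentence goes on to contrast this with a merely transient effect during the intervention. The Design Issues section makes a larger sustained decline in intervention teams the principal question.

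The timing rules are in other sections:

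- Intervention: "The intervention period was defined as the 14 months in which eligible patients were being identified and offered encounters with the pharmacists". Eligibility is determined at the start and "again at 3, 6, 9, and 12 months", and "Enrollment of patients occurred during months 1-14".
- Encounters with the pharmacist: "Follow-up appointments were to be scheduled weekly if adherence issues were being addressed and every three weeks if medication changes were being made".
- Discharge Criteria: patients leave when several criteria are met, when lost to follow-up, on declining further participation, or when "enrolled for 6 months without achieving blood pressure target (and no progress in any area was being made". The 6-month rule needs both conditions, so it does not cap the stay.
- Reentry: after a three-month gap, discharged patients who are eligible again "were allowed to reenter the program for additional adherence and/or intensification assistance".
- Design Issues: the article acknowledges only the opposite timing problem, that patients treated early "thus may be as much as 1 year out from the intervention when the 6 month post-intervention period ends". It adds a secondary analysis of blood pressure in the first and second three months after activation, with activation dates assigned at random to controls.

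**The concern.** A post-intervention window can show persistence only if, for most patients, it opens some time after treatment ended. Here it opens at the end of the enrollment period, with no washout. A patient activated near month 14 contributes readings from the weeks and months just after first contact, and a patient activated in month 1 contributes readings more than a year later. The primary interaction term pools them.

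What is at stake is the interpretation. The article addresses a health center director deciding whether to invest in the program. With pooled lags, a positive result could come from a lasting effect or from a larger effect that fades within a year of activation, and the primary contrast cannot tell these apart. The secondary activation analysis does not help, because it stops at 6 months after activation.

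**Working it through.** **Inputs from the article.** The intervention period is months 0-14 and enrollment runs through month 14 (Intervention). The post window is therefore months 14-20 (Primary Outcome). There is no maximum stay (Discharge Criteria). The stated detectable difference is 4.4 mmHg at power 0.8, with 275 patients per team and an ICC of 0.02 (Sample Size).

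**Assumptions, not in the article.** Activation is uniform over months 0-14, and readings are spread evenly over the window. The effect is constant for L months after activation and zero afterwards.

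**The plan's own figure.** The 4.4 mmHg serves here only as a yardstick. It can be back-solved but not reproduced, because the SD of change, alpha and sidedness are not stated. The design effect is 1 + (275 − 1) × 0.02 = 6.48, and the effective n per arm is 8 × 275 / 6.48 = 339.5. At an assumed two-sided 0.05 with a normal test, 4.4 mmHg corresponds to an SD of change of about 20.5 mmHg. The point does not depend on this.

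**Step 1: time since activation in the window.** A patient activated in month a is observed from 14 − a to 20 − a months after activation.

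| Activated in month | Months since activation in the window |
|---|---|
| 14 | 0-6 |
| 12 | 2-8 |
| 1 | 13-19 |

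So patients activated in months 12-14 are seen at 0-8 months. That largely coincides with the 0-6 months that the secondary analysis uses for the short-term effect.

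**Step 2: share of a fading effect left in the primary contrast.** For a patient activated in month a, the fraction of the window within L months of activation is min(a + L − 14, 6)/6, or zero if negative. Integrate over a and divide by 14:

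- L = 6: patients with a from 8 to 14 contribute 6 × 0.5 = 3, and 3/14 = 21%.
- L = 9: a from 5 to 11 contributes 3 and a from 11 to 14 contributes 3, and 6/14 = 43%.
- L = 12: a from 2 to 8 contributes 3 and a from 8 to 14 contributes 6, and 9/14 = 64%.

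**Step 3: effect needed for a window average of 4.4 mmHg.** L = 6: 4.4/0.214 = 20.5 mmHg. L = 9: 4.4/0.429 = 10.3 mmHg. L = 12: 4.4/0.643 = 6.8 mmHg.

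**Step 4: front-loaded enrollment.** If half of the patients are activated at month 0 and the rest uniformly over months 0-14, the shares halve to about 11%, 21% and 32%. If the other half falls uniformly in months 3-14, the first two become 0.5 × 3/11 = 14% and 0.5 × 6/11 = 27%.

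**Step 5: if encounters continued past month 14.** With uniform enrollment, a stay of S months (S up to 6) leaves S/14 of enrollees on the program when the window opens, and (S/14) × (S/2)/6 of window patient-time on the program. A 3-month stay gives 21% and 5%; a 6-month stay gives 43% and 21%. A patient enrolled at month 14 with a 6-month stay would be on the program for the whole window.

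**The case against.** **The sentence claims little.** Its verb is suggest, and its contrast is with an effect during the intervention. If encounters ended at month 14, every post-window reading does follow the intervention period. This stands as a reading of the second half of the sentence. It does not rescue the word *ensure* or the step to a persistent effect, since late-activated patients are then seen only in the first months after contact.

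**Treatment during the window is not documented.** A reader might infer that late enrollees were treated throughout the post window. The article does not say so. The intervention period is defined by when encounters were offered, and Design Issues describes re-enrollment after that period as what would follow if the program were ongoing, which points toward closure. The figures in Step 5 are therefore conditional.

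**The sizes are assumptions.** This stands. Neither the activation distribution nor the length of stay is given, and the first eligibility pull may well have been the largest. A short-lived effect would be heavily diluted: one gone at 6 months would need about 20.5 mmHg to average 4.4. The realistic risk is an effect that fades over 9 to 12 months. Including contacted patients who never enrolled reduces the absolute effect, but not the shares in Step 2.

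**A null result hiding an early effect is already handled.** This stands. The secondary activation analysis addresses that case, so it is not part of this point. The remark about being up to a year out enters no analysis and is not pressed either.

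**Conclusion.** The stated timeline does not support the claim that the windows ensure persistence. With enrollment to month 14, no stated washout or maximum stay, and re-entry allowed, the post window mixes patients from 0 to about 20 months after activation. Under uniform activation, an effect gone by 6, 9 or 12 months keeps about 21%, 43% or 64% of its size in the primary contrast. With half of activation at month 0 and the rest uniform over months 0-14, the shares are about half of these.

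A reader might go further and infer that the primary test is biased, or that a positive result would be a transient effect mislabeled. The article supports neither. The team-level randomized comparison is valid for the effect in months 14-20 whatever the mix of lags, and a truly lasting effect would also give a positive result. The fault is limited to the persistence reading.

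**What to change.** 1. Keep the primary test. Replace the guarantee of persistence with a description such as the effect in the 6 months after outreach closed.
2. State whether encounters continued past month 14. Reconcile the 14-month period with the passage in Design Issues that calls it a year, because this sets when the post window opens.
3. Pre-specify the treatment-by-period effect by activation timing, early versus late, using the randomly assigned control activation dates already planned. Activation date is a better index than the quarter of first eligibility, because uncontacted patients are dropped at quarter end and may be listed again.
4. Rest any persistence statement on the early-activated patients.
5. From the Medication Management Tool, report the share of intervention-arm post-window readings taken while a patient was still open or had re-entered. This also shows how clean the early group is. At VA sites it covers only patients who consented to this use of their program data (Settings).

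The cost is wording and one pre-specified interaction on data already held. The timing-specific estimates will have wider intervals, with only 16 teams, and early and late patients may differ in case mix as well as lag. The persistence claim becomes more modest.
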